| **Population: Inclusion of special groups (Check all that apply):**   | Gender  Male  Female  Age  0 – 4 years  5 – 9 years  10 – 19 years  20 – 64 years  65 + | Pregnant Women  Fetuses  Prisoners  Destitutes  Service Providers  Cognitively Impaired  CSW  Others (Parents)  Animal | | --- | --- |   NOTE It is the policy of the Centre to include men, women, and children in all research projects involving human subjects unless a clear and compelling rationale and justification (e.g. gender specific or inappropriate with respect to the purpose of the research) is there. Justification should be provided in the `Sample Size’ section of the protocol in case inclusiveness of study participants is not proposed in the study. | | | | | | |
| **Project/study Site (Check all the apply):**  Dhaka Hospital  Matlab Hospital  Matlab DSS Area  Matlab non-DSS Area  Mirzapur  Dhaka Community  Chakaria  Abhoynagar | | Mirsarai  Patyia  Other areas in Bangladesh Mirpur, Kamalapur, Sylhet  Outside Bangladesh  Name of Country:  Multi Centre Trial  (Name other countries involved): | | | | |
| Type of Study (Check all that apply):   | Case Control Study  Community-based Trial/Intervention  Program Project (Umbrella)  Secondary Data Analysis  Clinical Trial (Hospital/Clinic)  Family Follow-up Study | Cross Sectional Survey  Longitudinal Study (cohort or follow-up)  Record Review  Prophylactic Trial  Surveillance/Monitoring  Others: | | --- | --- |   NOTE: Does the study meet the definition of clinical studies/trials given by the International Committee of Medical Journal Editors (ICMJE)? Yes  No    Please note that the ICMJE defined clinical trial as “*Any research project that prospectively assigns human subjects to intervention and comparison groups to study the cause-and-effect relationship between a medical intervention and a health outcome*”.    If YES, after approval of the ERC, the PI should complete and send the relevant form to provide required information about the research protocol to the Committee Coordination Secretariat for registration of the study into websites, preferably at the [www.clinicaltrials.gov](http://www.clinicaltrials.gov/). It may please be noted that the PI would require to provide subsequent updates of the research protocol for updating protocol information in the website. | | | | | | |
| **Targeted Population (Check all that apply):**  No ethnic selection (Bangladeshi)  Bangalee  Tribal group | | Expatriates  Immigrants  Refugee | | | | |
| **Consent Process (Check all that apply):**  Written  Oral  None | | Bengali Language  English Language | | | | |
| **Proposed Sample Size:**  Sub-group (Name of subgroup (e.g. Men, Women) and Number   | Name | Number | Name | Number | | --- | --- | --- | --- | | (1) Rural | 960 | (3) City corporations slums | 640 | | (2) Urban municipalities | 960 | (4) City corporation non-slum | 640 |   Total sample size: 3200 | | | | | | |
| **Determination of Risk: Does the Research Involve (**Check all that apply**):**   | Human exposure to radioactive agents?  Fetal tissue or abortus?  Investigational new device?  (specify:      )  Existing data available from Co-investigator | Human exposure to infectious agents?  Investigational new drug  Existing data available via public archives/sources  Pathological or diagnostic clinical specimen only  Observation of public behaviour  New treatment regime | | --- | --- | | | | | | | |
| **Could the information recorded about the individual if it became known outside of the research:**   | Yes | No | Is the information recorded in such a manner that study participants can be identified from information provided directly or through identifiers linked to the study participants? | | --- | --- | --- | | Yes | No | Does the research deal with sensitive aspects of the study participants’ behaviour; sexual behaviour, alcohol use or illegal conduct such as drug use? |  | Yes | No | Place the study participants at risk of criminal or civil liability? | | --- | --- | --- | | Yes | No | Damage the study participants’ financial standing, reputation or employability, social rejection, lead to stigma, divorce etc.? | | | | | | | |
| **Do you consider this research (Check one):**  Greater than minimal risk  No more than minimal risk  Only part of the diagnostic test  Minimal Risk is "a risk where the probability and magnitude of harm or discomfort anticipated in the proposed research are not greater in and of themselves than those ordinarily encountered in daily life or during the performance of routine physical, psychological examinations or tests. For example, risk of drawing a small amount of blood from a healthy individual for research purposes is no greater than the risk of doing so as a part of routine physical examination". | | | | | | |
| **Yes/ No**  Is the proposal funded?  If yes, sponsor Name: (1) Bill and Melinda Gates Foundation    (2) | | | | | | |

Appendix 5: Detailed Budget

Appendix 6: Questionnaire

[Check-List](#__RefHeading___Toc132346870)

Check here if appendix is included

| Project Summary Describe in concise terms, the hypothesis, objectives, and the relevant background of the project. Also describe concisely the experimental design and research methods for achieving the objectives. This description will serve as a succinct and precise and accurate description of the proposed research is required. This summary must be understandable and interpretable when removed from the main application. **(Please keep as brief as possible).** |
| --- |
| Principal Investigator(s): [name] |
| Research Protocol Title: Monitoring the Impact of the SUZY Project role-out of Zinc as a Treatment for Childhood Diarrhea |
| Total Budget US$: 208,423 Beginning Date : 01/09/06 Ending Date: 15/06/07 |
| This is a repeat, ecologic survey to document changes in zinc coverage for childhood diarrhea, coinciding with the national roll-out of “Baby Zinc”. The surveys have been stratified by location; rural, urban municipalities, and city coprportation slum and non-slum populations.  In addition to zinc coverage, the surveys will monitor changes in the use of ORS or antibiotics, expenditures on diarrheal illnesses and other management practices. The surveys have been powered to identify disparities in care based upon gender, income and location of households.  The survey field sites have been purposively selected in order to facilitate comparisons with the baseline national coverage survey carried out in 2003/4. These include rural upazilla (Mirsarai, Abhoynagar, Hobiganj), urban municipalities (Khulna, Sylhet, Camila), and City Corporation zones (slum: kamalapur, Mirpur and non-slum Green--------- The same interviewer administered questionnaire will be used.  The results of this study will provide guidance for public, private and NGO delivery systems as they jointly endeavor to reach all under-five children with zinc treatment of any diarrheal disease episode. |
| KEY PERSONNEL (List names of all investigators including PI and their respective specialties)     | Name | Professional Discipline/ Specialty | Role in the Project | | --- | --- | --- | | 1. [name] | Health services research | PI | | 1. [name] | Statistician | analyses, data management | | 1. [name] | Field studies | Coordination of survey conduct | |

# Description of the Research Project

##

## Hypothesis to be Tested:

Concisely list in order, the hypothesis to be tested and the Specific Aims of the proposed study. Provide the scientific basis of the hypothesis, critically examining the observations leading to the formulation of the hypothesis.

Over the planned 8 months of observation;

H1: That there will be a significant, upward trend in use of zinc for the treatment of childhood diarrhea.

H2: That there will be a significant downward trend in the use of antibiotics for the treatment of non-bloody childhood diarrhea

H3: That there will be disparities in zinc treatment coverage on the basis of household income status. gender oand location (rural, urban, city corporation slum and non-slum populations).

## Specific Aims:

Describe the specific aims of the proposed study. State the specific parameters, biological functions/ rates/ processes that will be assessed by specific methods.

Coinciding with the health care provider promotion and mass media marketing of "Baby Zinc" for the treatment of childhood diarrhea,

1. To monitor the proportion of under-five diarrheal episodes receiving zinc treatment and changes

over time.

2. To document changes in provider and caretaker practices. Included here are the use of ORS,

antibiotics, antidiarrheal and other prescribed treatments.

3. To monitor changes in household expenditures on diarrheal illnesses.

4. To monitor for disparities in zinc coverage by household income status, gender and location.

5. To assess impact in terms of need for/utilization of clinical services and hospitalizations.

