## Background of the Project including Preliminary Observations

Describe the relevant background of the proposed study. Discuss the previous related works on the subject by citing specific references. Describe logically how the present hypothesis is supported by the relevant background observations including any preliminary results that may be available. Critically analyze available knowledge in the field of the proposed study and discuss the questions and gaps in the knowledge that need to be fulfilled to achieve the proposed goals. Provide scientific validity of the hypothesis on the basis of background information. If there is no sufficient information on the subject, indicate the need to develop new knowledge. Also include the significance and rationale of the proposed work by specifically discussing how these accomplishments will bring benefit to human health in relation to biomedical, social, and environmental perspectives.

Zinc deficiency has been found to be widespread among children in developing countries, occurring throughout Latin America, Africa, the Middle East and South Asia. It has been estimated that the annual Disability Adjusted Life Years (DALYs) lost due to zinc deficiency is over 57 million (1) . Children between 6 months to 5 years of age who receive zinc for the treatment of a diarrheal illness (20 mg/day for 10 days) recover faster, have a 30% reduction in the likelihood of developing prolonged diarrhea, and have an estimated 50% reduction in non-injury mortality over the next 6 months (2-8). In response to this evidence, WHO/UNICEF revised its childhood diarrhea management recommendations to include zinc in the treatment of any under-five child with a diarrheal illness (9). This evidence also sstimulated the develpoment of the Gates Foundation funded Scale Up of Zinc for Young Chuildren (SUZY) Project. The SUZY Project is now into its fourth and final year. The national roll-out of a zinc providedr promotion and mass media campaign in support of “baby zinc” is scheduled to begin in late September or early October, 2006.

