Within each cluster a household census survey will be completed for the identification of any under -five child who has had a diarrheal ilness in the past two weeks of at least 2 days duration. The aim is to identify 16 cases per cluster.

Within each site, random cluster selection will be repeated at the time of each new survey round. The sampling framework is summarized in figure 1.

CHILDREN UNDER FIVE YEARS OF AGE

Diarrheal Disease Episode in past 2 weeks and

at least 48 hrs duration

Dhaka Urban Municipalities Rural Upazillas

2 slum zones Khulna Abhoynagar

2 non-slum zones Camila Mirsarai

Sylhet Hobiganj

random random random

20 clusters 20 clusters 20 clusters

per zone per municipality per upazilla

at 16 casesper cluster

n=320 cases per site

N= 640 slum N=960 N=960

N= 640 non-slum urban municipal rural cases

per round per round per round

Figure 1. Summary of sampling frame for cluster surveys

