## Sample Size Calculation and Outcome Variable(s)

For each survey round (weeks 1 to10, 12 to 21 , 23 to 32 weeks) we are determining estimates of zinc, ORS and antibiotic use (prevalence). With each new interval we will be sampling from the same sites, but will carry out a new random selection of clusters in which cases will be identified.

As depicted in figure 1, for each survey round the number of subjects by site and location is as follows:

Location Sites N/site N/location

City corporations Slums x 2 320 640

Non-slums x 2 320 640

Urban Municipalities x 3 320 960

Rural Upazillas x 3 320 960

Based upon WHO EPI cluster survey methods, the design effect is estimated to be 2.0 (11)

a. Prevalence of zinc treatment by site: Setting confidence at 0.95 and a minimal detectable error of a 5% for a prevalence estimate within a site, assuming the baseline overall prevalence of zinc coverage to be 10%:

(Z alpha )2 (P)(1-P)

N/site = x 2 (cluster adjustment design effect)

d 2

N/site = 276 cases

b. Trends in use of ORS and antibiotics by site: Setting confidence at 0.95 and a minimal detectable error of 10% around a prevalence of 50% of cases being treated with ORS or an antibiotic;

N/site = 198

d. Comparison of two proportions (hypothesis testing):

To examine whether zinc coverage in urban or rural locations is significantly different among males vs females, setting the level of conficence at .95 (one-sided), power at .80, minimal detectable difference 10%, assuming an overall prevalence of 25% coverage by the third cycle

(Z alpha + Z beta)2 (P)(P-1) x 2

N/gender/location = x 2 (cluster adjustment design effect)

d 2

N/location = 461

Given these estimates, we will have the power to detect smaller differences in the rural and municipality

locations. In the City Corporations sites the power is adequate if we combine slum and non-slum populations. Keeping them separate will allow for a minimal detectable difference of 12%.

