## Ethical Assurance for Protection of Human Rights

Describe in the space provided the justifications for conducting this research in human subjects. If the study needs observations on sick individuals, provide sufficient reasons for using them. Indicate how subject’s rights are protected and if there is any benefit or risk to each subject of the study.

This study addresses childhood diarrhea, a major contributor to pediatric morbidity and mortality in Bangladesh. Zinc, in the doses to be prescribed in this study, is not known to cause any major, harmful health events. It may increase the likelihood of transient vomiting. Potential, minor side effects are favorably balanced by the proof of its effectiveness in reducing the length and severity of a diarrheal episode and the decreased risk of a subsequent episode. It has also been demonstrated to reduce subsequent mortality by 50%.

Parents of children with diarrhea will be interviewed once during or shortly after an episode. Any child found to be moderately to severely dehydrated or experiencing bloody diarrhea will be referred to the nearest MOHFW or NGO health facility.

This study is not prescribing treatment, but does promote its use through a mass media campaign and provider sensitization + training. It will monitor trends in treatment practice, with a focus on zinc as a treatment. All caretakers/parents interviewed will be requested a verbal consent.

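### Aim 5 seeks impact on need for services and hospitalisation, but the survey is described per case only, so a fall in the number of episodes would not show

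*Protocol*

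**What the plan says.** Protocol, Specific Aims, item 5: "To assess impact in terms of need for/utilization of clinical services and hospitalizations".

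Protocol, Research Design and Methods, describes case finding: "Within each cluster a household census survey will be completed for the identification of any under -five child who has had a diarrheal ilness". To be eligible, the illness must fall within the preceding fortnight and have lasted two days or more. The target follows: "The aim is to identify 16 cases per cluster". The sampling figure carries this through as "n=320 cases per site", and clusters are drawn afresh within each site for every round.

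The Sample Size section sizes the use of zinc, ORS and antibiotics among cases, and a gender comparison of zinc coverage. It contains no calculation for service use or hospitalisation. The Measurement paragraph limits the management and expenditure questions to the identified case. Data Analysis plans regressions of care seeking and of treatments received.

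On how zinc works, Ethical Assurance cites its "effectiveness in reducing the length and severity of a diarrheal episode and the decreased risk of a subsequent episode". The Background says that treated children "have a 30% reduction in the likelihood of developing prolonged diarrhea".

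**The concern.** Need for services in a population depends on how many children fall ill and on what happens in each illness. The protocol credits zinc with both kinds of effect: shorter and milder episodes, and fewer later ones. A sample made up of ill children, filled to about the same number each round, can reflect only the second component. If fewer children fall ill, the numerator and the denominator of a per-case proportion shrink together and the proportion stays where it was.

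The results are meant to guide public, private and NGO delivery systems. A flat proportion hospitalised, reported under an aim worded as impact, could be read as the scale-up having no effect. An analysis plan cannot repair this later, because a count of screened children that was not taken in the field cannot be recovered.

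**Working it through.** **1. The plan's own numbers.** 20 clusters x 16 cases = 320 per site, and 10 sites x 320 = 3200 per round, as stated. The zinc precision figure is 1.96² x 0.10 x 0.90 / 0.05² x 2 = 276.6 (stated 276). The gender comparison is (1.645 + 0.842)² x 0.25 x 0.75 x 2 / 0.10² x 2 = about 464 per gender (stated 461). Both reproduce, and both are proportions among cases.

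**2. Does a fall in episodes show?** The protocol gives neither a two-week prevalence nor a hospitalisation rate. Assume a prevalence of 10%, 2% of cases hospitalised, 16 cases reached in each cluster, and a 20% fall in illness with nothing else changed.

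| | Before | After |
|---|---|---|
| Two-week prevalence | 10% | 8% |
| Cases surveyed | 3200 | 3200 |
| Hospitalised among them (2%) | 64 | 64 |
| Per-case proportion | 2.0% | 2.0% |
| Under-fives screened per 16 cases | 16/0.10 = 160 | 16/0.08 = 200 |
| Under-fives screened per round | 32,000 | 40,000 |
| Hospitalised per 1000 under-fives | 2.0 | 1.6 |

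Only the screening effort moves, and the protocol does not say that it is recorded. The per-case proportion also stays constant for any prevalence of 5-15%, 1-5% hospitalised and falls of 10-30%, because it does not depend on prevalence. If the census were instead completed and every case taken, the case count could vary. Clusters are redrawn each round, however, so raw counts would still need a child denominator.

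**3. The two-day entry rule.** If 10% or 20% of episodes, none of them hospitalised, shorten to below two days and drop out, the per-case proportion rises from 2.0% to 0.02/0.90 = 2.2% or 0.02/0.80 = 2.5%. A benefit would then look like a deterioration.

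**4. Per-case hospitalisation, illustration only.** Assume that coverage goes from 10% to 25% and that the 30% reduction in prolonged diarrhoea applies unchanged to hospitalisation. The relative level is (1 - 0.30 x 0.25) / (1 - 0.30 x 0.10) = 0.925/0.970 = 0.954, a fall of 4.6%. The 95% half-width for a difference between two full rounds at design effect 2 is 1.96 x sqrt(2 x 2 x p(1-p)/3200).

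| Assumed hospitalised (p) | Expected change (points) | Half-width (points) |
|---|---|---|
| 2% | 0.09 | 0.97 |
| 5% | 0.23 | 1.51 |
| 10% | 0.46 | 2.08 |

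Even a 30% relative fall per case, with 3200/2 = 1600 effective cases per round and a two-sided 5% test, has power of 0.15, 0.26 and 0.56 at 1%, 2% and 5% hospitalised.

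**5. What a tally would add.** At prevalences of 5%, 10% and 15%, 3200 cases correspond to about 64,000, 32,000 and 21,300 under-fives. With a design effect of 2 (assumed to hold here too), power for a 10% relative fall in illness between two rounds is about 0.85 to 0.88 over all sites. For a 20% fall within a single site it is only about 0.49 to 0.53.

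**The case against.** Much can be said for the plan.

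- **The number 16 is an aim.** No stopping rule is given, and a census that will be completed could supply a child count. A reader might infer that teams search on until they have 16, or that no denominator can exist. The text supports neither. What stands is that counting under-fives is not stated, and that 16 is the working number behind every total.
- **Service use per episode is estimable.** The baseline survey reported it, and regressions of care seeking are planned. Milder and shorter illness can lower need within a case, and the Background reports longer duration as a predictor of seeing a licensed allopath. A reader might infer that Aim 5 cannot be answered at all; that goes too far. What cannot be seen is the effect through fewer episodes.
- **The illustration rests on assumptions.** The 10% and 25% coverage figures come from separate sample size calculations and are not presented as a planned rise. The 30% refers to prolonged diarrhoea. No hospitalisation rate is given. The ratio of half-width to change is therefore not a protocol figure, and provider visits were not computed.
- **No hypothesis or stated test is tied to Aim 5.** Nothing says that a flat proportion will be reported as no impact. The misreading is a risk, not a plan.
- **The questionnaire is not in the text at hand.** A household roster or hospitalisation items cannot be ruled out. That would ease the fix, but the protocol would still need to state the denominator and its use.
- **Rates per 1000 would not prove impact.** This stands in full and shapes the fix.

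**Conclusion.** The point holds in a limited form. As written, the survey can describe service use and hospitalisation per eligible episode. It cannot assess population need or the population effect on hospitalisation, because a fall in episodes leaves per-case proportions unchanged and no child denominator is stated. An unchanged per-case hospitalisation proportion would not be evidence of no impact. This follows from the structure of the sample and needs no assumed rate.

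The sizes do need assumptions. With 2-10% of cases hospitalised, the 30% effect carried over and coverage going from 10% to 25%, the per-case change is 0.1-0.5 points against a half-width of 1.0-2.1 points. That shows how weak the per-case route might be; it does not forecast the result. The coverage estimates for zinc, ORS and antibiotics among cases are not touched. The change is worth making because it is cheap and must come before fieldwork.

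**What to change.** 1. In the census already planned, record for each cluster and round the number of households and under-fives screened, and whether screening was completed or stopped once 16 cases were found.
2. Report eligible diarrhoea, provider visits and hospitalisations per 1000 under-fives screened, next to the per-case figures.
3. Reword Aim 5, for example: to describe per-episode and per-child utilisation of clinical services and hospitalisation by survey round.
4. State that neither a change nor the absence of one will be attributed to the zinc roll-out, because the rounds fall in different seasons between September and April and there is no comparison area.

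The cost is a tally sheet per cluster, a little more field time and one reworded aim. The study gives up the claim to measure impact under Aim 5.
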